### Intervention

Those randomized to transfusion will receive the standard-of-care-ordered RBC transfusion. This means that they will receive the transfusion as specifically ordered by their primary physician, typically one to two units of allogeneic RBCs. Those randomized to the no-transfusion arm will be discharged from the AIC without receiving an RBC transfusion. The patients who are randomized into the transfusion group will be crossed over into the no-transfusion group and the patients who are randomized into the no-transfusion group will be crossed over into the transfusion group at a subsequent visit. The time of this crossover for a given patient will be at their next scheduled transfusion that is no less than 1 week from the time of their most recent RBC transfusion in this trial.

### Blinding

Due to the nature of the intervention (transfusion versus no transfusion), blinding to the intervention will not be feasible for either the patient or the clinical team in this pilot clinical trial. The accelerometer does not provide any visual indication of activity levels (e.g., no step count or estimated energy expenditures), so participants will be blinded to the data accumulated by the device. With the exception of the Data Monitoring Committee, investigators will not have access to the accelerometer data until the completion of the trial. Patients may access their data after completion of the trial by request to the study team. Because blinding to the intervention is impossible, and because the purpose of the trial is carefully explained to participants beforehand, we note the potential for both performance and detection biases. In particular, many participants may have an expectation of lower functional status after a no-transfusion encounter. One downstream consequence of this is a potential bias towards lack of effect, meaning that transfusions may be biased to appear more effective than the no-transfusion intervention. Concerns related to selection bias are expected to be largely mitigated by randomization and by the crossover nature of the design. Nonetheless, risks related to residual biases resulting from unique characteristics associated with patients who consent to participate in this trial clearly remain.

### Measures

The primary outcome measure of this study is the estimated daily energy expenditure using, e.g., the Williams Work-Energy Approximation calculated from acceleration-based activity counts and body weight. We choose this metric because it has been shown to be correlated with energy expenditure estimations from indirect calorimetry, is a clear indicator of activity level and has been well studied in the medical literature [17, 19–22, 24]. We emphasize that our study design seeks to measure changes in activity levels, thus the absolute accuracy of the energy expended by a participant is not critical to our broader clinical question. Secondary outcome measures include daily step count, daily sedentary time, MET rate, and PROMIS Global 10 Survey results. This survey is a ten-question assessment designed to measure overall physical, mental, and social health as well as pain, fatigue, and perceived QoL. Further exploratory outcome measures will consider activity bout counts, estimated energy expenditure on a more finely resolved time scale (e.g., minute to minute), nonintervention RBC transfusions, and need for hospital admission or other health care encounters.

### Data collection and management

#### Sources and repositories

There are five sources of data in this trial – base data collected by the devices, derived data interpreted by the device analysis software, weekly survey data collected via telephone, study participation data such as Consent Forms, and finally, encounter-associated data such as SC encounter notes or laboratory results measured in the AIC.

During the enrollment and data collection phases of the study, the primary data repository will be a set of hard copy study participant files that will be maintained by the lead SC at the AIC. A centralized digital data store (CDS) will also be maintained at an access-restricted and access-logged study site within Mayo Clinic’s secure network. As the study progresses and patient data are recovered from devices, this raw device data will be added to the CDS. In order to facilitate ease of interpretation and analysis after collection, the CDS will also be tied to a REDCap store. Only those with approved access to the REDCap data management system will have access to the study data. Telephone survey and AIC encounter data will also be transferred from the hard copy files into REDCap by the SC.

During the analysis phase, all derived data and global study result data will also be stored in the CDS. Upon study data collection completion, all relevant physical files not yet present in the CDS will be scanned and integrated into the digital store. Physical files will be held and then disposed of according to the Mayo Clinic record retention policy. The primary repository of data for analysis and reporting will thus be the CDS.

### Practice logistics and workflow

A critical component for the successful completion of this study is close integration with the current hematology and oncology practices at the AIC. From a practical perspective, engineering this integration has been the most challenging aspect of moving the study forward. Because of this, we detail our practice logistics and workflow model.

It is important to remember that in this protocol *not* transfusing the patient is the intervention – otherwise standard practice is followed. Thus, from a practice logistics and patient safety point of view it is during the no-transfusion arm that special care must be taken.

The current practice at the AIC is for patients receiving transfusion therapies (e.g., chemotherapy) to be associated with a set of standing orders by their practicing physician. These standing orders are typically directions to transfuse the patient when their Hgb is measured below a specific level. For many practicing physicians this Hgb level will be between 7.0 and 9.0 g/dL. These standing orders are specified for a defined time period up to 3 months so their modification is an important aspect of implementing the proposed protocol.

When a SC identifies a patient who appears to be a likely candidate, they will contact the potential study participant’s primary physician to receive conditional approval for inclusion in the study. Patients receiving conditional provider approval will have Hgb levels monitored on the day of their AIC visit by the SC. If the Hgb is within the range prescribed for transfusion, the patient is approached for screening and informed consent. If enrolled, the SC will randomize the participant. If the participant’s next encounter is to transfuse, no change to the standing orders is required.

If the patient’s next encounter is no-transfusion, new standing orders are requested. These orders are designed to avoid RBC transfusion unless specific “over-riding” RBC transfusion criteria are present. These “over-riding” RBC transfusion criteria include: acute ischemia (e.g., MI, CVA), Hgb <7.0 g/dL, active bleeding, and symptomatic anemia (hypotension, tachycardia, angina or syncope/presyncope believed related to anemia). If none of the above mentioned “over-riding” RBC transfusion criteria are present, the patient will not be transfused.

After the participant crosses from one study arm to the other, the SC requests new standing orders as necessary.

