### Participants and screening

Study participants will be identified in the Ambulatory Infusion Center (AIC) of a tertiary care medical center. The study population will consist of adult (aged 18 years or older) male and female hematology and oncology patients presenting to the AIC with anemia (Hgb under practice standard threshold for transfusion, e.g., 7.0–9.0 g/dL) and who are planned to undergo routine RBC transfusion. Subjects with at least one prior presentation to the AIC within 3 months of the screening visit will be eligible for study participation. This inclusion criterion has been selected due to the fact that our preliminary research indicates that those who present to the AIC on more than one occasion for RBC transfusion are highly likely to present for a subsequent RBC transfusion in a 28-day time frame. A full list of the inclusion and exclusion criteria are provided in Table 1.

**Table 1 Tab1:** Inclusion and exclusion criteria

Inclusion criteria	Exclusion criteria
Age ≥18 years	Refusal to provide informed consent
At least one prior encounter in the AIC	Refusal by the health care team
Planned RBC transfusion	Acute ischemia (e.g., myocardial infarction (MI), cerebrovascular accident (CVA))
	Hgb <7.0 g/dL
	Active bleeding
	Symptomatic anemia (hypotension, tachycardia, angina, syncope/presyncope believed related to anemia)
	Nonambulatory functional status
	Established or uncertain pregnancy status

*AIC* Ambulatory Infusion Center, *RBC* red blood cell

For the exclusion criteria of pregnancy, potential study participants in the reproductive age group will be asked if they might be pregnant. If the response is “yes” or “unknown,” the potential study participant will be excluded. Screening/consent logs will be maintained centrally to allow generation of a CONSORT diagram, but will also made available to the transfusion medicine service at Mayo Clinic in Phoenix, AZ, USA to facilitate the procedures outlined below. Consenting participants will be provided with an accelerometer to wear continuously for the duration of their involvement in the trial (28 days). This device, described further below, will automatically capture relevant physiological data with no need for intervention by the patient. Following the trial, participants return the device by mail and data are retrieved by the investigative team.

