### Randomization

After informed consent has been obtained, study participants will be stratified into those that are actively receiving chemotherapy and those that are not. Within each stratum, participants will be randomized using simple randomization (Pr(transfusion group first) = 0.5). Patients successfully enrolled will be randomized to one of two transfusion/no transfusion sequences (Fig. 1). The SC will obtain the randomized sequence from the Research Electronic and Data Capture (REDCap) randomization module. After randomization, the SC will inform the AIC of the appropriate timing of the no-transfusion study period so that an updated order set can be prepared. It is recognized that using simple randomization may result in imbalances in the transfusion sequences, but simple randomization was selected for this study for ease of implementation. The crossover design also helps mitigate confounding provided that there is no period effect observed in the data.

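### The physician's approval before randomization is only conditional, and the no-transfusion orders are requested once the sequence is known, so a refusal made with knowledge of the allocation before the first visit can arise in one sequence only

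*Protocol article*

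**What the plan says.** Table 1 (Participants and screening) lists "Refusal by the health care team" among the exclusion criteria and gives it no time limit.

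The Practice logistics and workflow section sets the order of steps. The coordinator first contacts the patient's "primary physician to receive conditional approval for inclusion in the study". The hemoglobin check on the day and informed consent follow, and then "If enrolled, the SC will randomize the participant". From there the two sequences are handled differently:

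- Transfusion first: "If the participant’s next encounter is to transfuse, no change to the standing orders is required".
- No transfusion first: if the "next encounter is no-transfusion, new standing orders are requested".

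The section closes by saying that further orders are requested as needed once a participant has crossed over. The Randomization section has the same timing: the infusion center learns when the no-transfusion period falls only once randomization is done, and the changed orders are drawn up from there.

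The Blinding section states that the clinical team is not blinded. It also says: "Concerns related to selection bias are expected to be largely mitigated by randomization and by the crossover nature of the design". The Primary analysis section uses an as-treated set, the Data monitoring section removes participants whose data are lost through partial completion, and the sample size section wants 12 per group to complete the first randomized phase.

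**The concern.** In this trial, withholding blood is the intervention, and it needs an order from the patient's own physician. That order is sought after allocation from someone who knows the allocation, and before the first visit it is needed in one sequence only. The approval obtained earlier is called conditional. The condition is not defined, and nothing says that the approval binds the physician to the later orders.

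A physician who hesitates over a particular patient could therefore agree to inclusion and then decline the orders on learning that the first visit is a no-transfusion visit. A comparable patient assigned to transfusion first would meet no such decision before completing the first phase. At stake are the balance of the first randomized phase, on which the sample size is built, and how selected the final sample becomes. The Blinding section counts on randomization to limit selection bias, but randomization cannot guard against selection that follows it.

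**Working it through.** **Order of steps**

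| Step | Transfusion first | No transfusion first |
|---|---|---|
| Conditional approval | before allocation | before allocation |
| Hemoglobin check, consent, randomization | same | same |
| Physician's orders needed before visit 1 | none | new no-transfusion orders |
| Physician's orders needed at crossover | new no-transfusion orders | as necessary |

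Refusals in the first row cannot depend on sequence. A refusal in the third row can arise only in the right-hand column.

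**The plan's own figure**

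The plan wants 12 per group, so 24 evaluable. Raised by 25%, 24 × 1.25 = 30, which reproduces the planned total. Since 24/0.80 = 30, this allows for a 20% loss.

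**Illustration of a one-sided refusal**

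The inputs from the article are 30 participants and simple randomization with probability 0.5 for each sequence, so 15 are expected in each. The refusal rate r among those assigned to no transfusion first is not in the article; I assume 5% to 30%.

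- Expected number remaining in that sequence: 15 × (1 − r).
- Chance that at least 12 remain: upper tail at 12 of a binomial with n = 30 and p = 0.5 × (1 − r).
- Chance of at least one such refusal: 1 − (1 − r/2)^30.

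| Assumed r | Expected remaining | Chance of at least 12 | Chance of at least one refusal |
|---|---|---|---|
| 0% | 15 | 0.900 | 0 |
| 5% | 14.25 | 0.843 | 0.532 |
| 10% | 13.5 | 0.767 | 0.785 |
| 20% | 12.0 | 0.569 | 0.958 |
| 30% | 10.5 | 0.345 | 0.992 |

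The transfusion-first sequence stays at 15 expected and 0.900 throughout. No other attrition is counted here. If the 20% loss that the plan allows for also occurs in both sequences, 10% refusal leaves 13.5 × 0.80 = 10.8 against 12.

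**Shift in the unadjusted first-phase mean**

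If refused patients are d standard deviations less active than those retained, the mean of the retained group moves by r × d. With assumed values this is 0.05 × 0.5 = 0.025 SD at the low end and 0.20 × 1.0 = 0.20 SD at the high end. For scale, the standard error of a comparison of 15 with 12 is √(1/15 + 1/12) = 0.39 SD. The shift concerns an unadjusted group mean, which is not what the primary model estimates.

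**The case against.** The conditional approval comes before consent and randomization and is the evident place for most refusals; those favor neither sequence. The condition may simply mean the hemoglobin result and consent. The workflow also states that, absent the over-riding criteria, the participant is not transfused, and it describes no veto by the physician after allocation. This stands in part: the article does not describe such a refusal, but it neither rules one out nor makes the approval binding.

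A reader might infer that the physician may invoke the Table 1 exclusion after seeing the allocation. The text does not say that declining the orders triggers that exclusion. A reader might also infer that all refusals before the first visit fall in one sequence. Those at the approval step do not.

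The crossover answers much of the bias argument. Transfusion-first participants meet the same request at crossover, and partial completers are removed from either sequence, so completers contribute both kinds of visit. The participant random effect and the 3-day baseline absorb much of any difference in activity level. Bias in the treatment contrast would need more than that, for instance that refused patients respond differently to transfusion. This stands. What it leaves is the asymmetry in the first phase, where the plan counts its 12 per group, and a sample that may be more selected.

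An article may leave the handling of withdrawn approval to the full protocol. That is fair for the handling, but the order of steps is stated here in detail and is itself the weakness.

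**Conclusion.** The point holds as a weakness in the stated workflow. The decision that puts the no-transfusion assignment into effect is taken after allocation by an unblinded physician, and before the first visit it arises in one sequence only. Neither the as-treated analysis nor the removal of partial completers protects against a resulting switch or loss.

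The size cannot be fixed from the article. At assumed refusal rates of 5% to 30%, the expected loss is 0.75 to 4.5 of 15 participants, all from one sequence.

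A tempting further conclusion is that the remaining no-transfusion visits come from fitter patients and that the estimated benefit of transfusion is biased downward. The article does not support it. The shift of about 0.03 to 0.20 SD rests on two assumed inputs, applies to an unadjusted mean, and is at most about half a standard error (0.20/0.39). For the baseline-adjusted crossover estimate, both the size and the direction of any bias are unknown. The change is worth making because it closes a route to selection after allocation at almost no cost, not because harm has been shown.

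**What to change.** 1. Before randomization, obtain the primary physician's final approval, stated to cover both sequences.
2. Before randomization, have the study no-transfusion order set, with the over-riding criteria already in the protocol, prepared and agreed for whichever visit it will apply to. Randomize only then, and activate the orders for the assigned visit.
3. State that refusal by the health care team is an eligibility exclusion that applies only before randomization.
4. Count and report any later refusal by sequence, and keep those participants in their assigned sequence in a supporting as-randomized analysis alongside the as-treated one.

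This changes the timing and wording of the workflow and adds one supporting analysis. The downside is small: orders will be prepared for a few patients who then decline consent. No change to the clinical transfusion criteria is proposed.

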### Data monitoring

For this trial, data monitoring consists of measures required for patient privacy and to ensure the success of the trial. Privacy compliance will follow the standards set by both the Health Insurance Portability and Accountability Act (HIPAA) and by Mayo Clinic internal standards. To help ensure the accuracy of the study data, the Data Monitoring Committee of Drs. [name] and [name] will randomly sample and review the validity of data collected, especially device data. Throughout the trial ongoing assessment will monitor for device data loss, partial study completion, and other potentially unforeseen data concerns. In the event of data loss due to partial study completion, the patient will be removed from the cohort. In the event of data loss due to device issues or other unforeseen events the impact of the loss will be assessed by the investigators. If the loss compromises the integrity of the study the patient will be removed from the cohort. A valid device wear hour is defined as ≤30 min of consecutive “zero” values (no activity) and a valid day as ≥10 wear hours per day [25]. If the loss is consistent with reasonably acceptable missing data; for example, the subject forgetting to put the device on for an hour after bathing, then the missing data will be dealt with via appropriate statistical methods. These could include amongst others a Bayesian-based imputation or an all-available average, with the appropriate method chosen based on the nature of the missingness. Care will be taken to insure consistency across subjects and missing-data episodes.

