### Secondary

As a pilot trial we further delineate a set of secondary objectives. These are less formal than our primary objectives and are designed to gauge study feasibility, with a particular focus on scalability of methods to a potentially larger future trial. To that end we aim to evaluate the suitability of the ActiGraph wGT3X-BT for use in our target population. While the device has been validated in terms of its technical measurement [17–22], it remains an open question as to whether or not our patient population, most of whom are receiving chemotherapy or are transplant recipients, will display a level of adherence that is sufficient for answering our larger clinical question. We will also monitor enrollment volume, trial completion volume, device failure rates, and other such measures which might be of practical importance when considering scaling to a larger future trial.

In order to consider whether or not to move forward from a pilot trial to a larger future randomized clinical trial, we will carefully evaluate the results for a signal of efficacy. If there is strong evidence that RBC transfusion is efficacious in improving patient activity levels a larger trial is less likely to be considered. Alternatively, if there is evidence that “no transfusion” is better, or if the results are equivocal, we are more likely to pursue a larger trial. In addition to intervention efficacy, we will also assess both the feasibility of scaling the trial to a more definitive phase II/III design and the impact of any adverse events. We will carefully consider participant adherence rate and the potential for increasing enrollment as prerequisites for proceeding to a larger trial. Adverse events, if any, will be evaluated as outlined by the Safety and Monitoring Plan (Additional file 1). The final document reporting the results of this trial will follow the main Consolidated Standards of Reporting Trials (CONSORT) 2010 Statement: extension to randomized pilot and feasibility trials [23]. Both this trial and any future trial will follow the Standard Protocol Items: Recommendations for Interventional Trials (SPIRIT) Checklist (Additional file 2).

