### Sample size considerations and recruitment

This is a pilot study to determine whether accelerometers are sensitive enough to detect change in functional status in patients undergoing ambulatory transfusion services. The primary hypothesis is to detect change in total energy expenditure after the transfusion in both between and within individual comparisons. A minimum clinically relevant difference is not yet known for this outcome. To estimate the sample size, we approach the calculation from the perspective of having sufficient data to estimate the standard deviation so that we could plan a follow-up study. Julious [27] recommends studying 12 participants per group for such aims. We apply this recommendation to this study by assuming that we want at least 12 participants to complete the first randomized phase of the crossover design (i.e., the parallel group portion of the study). Based on this, we will want to have at least 24 subjects who will provide evaluable data from the activity monitor. We therefore adjust the sample size upwards by 25% to account for attrition and/or changes in the transfusion schedule. Thus, our total planned sample size is 30 participants. Preliminary research with clinicians familiar with the infusion center patient population suggests that an enrollment of this size should be readily achievable. Specific strategies for achieving adequate enrollment include presentations to the hematology and oncology practices in order to advertise the study to providers, as well as access to the Mayo Clinic patient scheduling and electronic health record system. This will ensure the ability to have sufficient on-site recruiting staff on days where patients known to be eligible are scheduled for transfusion.

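### Removing partial completers from the cohort discards first-phase data that the sample size counts as sufficient and the primary model can use, and risks selection after randomization

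*Protocol article*

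**What the plan says.** Under Data monitoring the protocol article sets an automatic rule: "In the event of data loss due to partial study completion, the patient will be removed from the cohort". Other losses are treated more flexibly there. Device problems are judged case by case, and short gaps may be imputed or averaged over what is available.

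Under Sample size considerations and recruitment the stated purpose is "having sufficient data to estimate the standard deviation so that we could plan a follow-up study". The plan applies a 12-per-group recommendation by wanting "at least 12 participants to complete the first randomized phase of the crossover design (i.e., the parallel group portion of the study"), and from this derives "at least 24 subjects who will provide evaluable data from the activity monitor". It then says it will "adjust the sample size upwards by 25% to account for attrition and/or changes in the transfusion schedule", so that "our total planned sample size is 30 participants".

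Under Primary analysis the model is a random effects model on daily energy expenditure, using the 7 days after each visit and adjusting for the 3 days before it. Under Intervention, crossover takes place at the next scheduled transfusion at least a week after the latest trial transfusion, with no upper limit. Under Participants and screening, eligible patients are said to be "highly likely to present for a subsequent RBC transfusion in a 28-day time frame". The secondary aims add: "We will also monitor enrollment volume, trial completion volume, device failure rates, and other such measures".

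**The concern.** Someone who finishes the first phase with good device data and never reaches the second visit meets the sample-size requirement and is deleted under the data-monitoring rule. Both statements cannot govern the same person.

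Three things are at stake. Usable data are lost from a trial of 30. The retained cohort is defined by an event after randomization: under Practice logistics and workflow, standing orders trigger transfusion when hemoglobin falls below a set level, and first-period transfusion is meant to change hemoglobin. Retention could therefore differ by sequence and by health, and the standard deviation that the pilot exists to estimate would then describe a selected group. Finally, completion and adherence inform the decision on a larger trial, and they would look better than they are if computed on the reduced cohort.

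**Working it through.** **1. The plan's own figure.** 2 × 12 = 24 evaluable; 24 × 1.25 = 30 enrolled. The stated 30 reproduces. It tolerates 30 − 24 = 6 losses, and 6/30 = 20%.

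**2. The three sections side by side, for a participant with a complete first phase and no second.**
- Sample size: counts toward the 12 per group.
- Primary analysis: contributes daily values from one visit, which a random effects model accepts.
- Data monitoring: removed.

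**3. Chance of keeping 24 under the removal rule.** No completion rate is given, so the probability p of completing both periods is an assumption, taken as common and independent across participants. With X ~ Binomial(30, p):

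| p | Expected kept, 30p | P(X ≥ 24) | N for an expected 24, 24/p rounded up |
|---|---|---|---|
| 90% | 27 | 0.97 | 27 |
| 85% | 25.5 | 0.85 | 29 |
| 80% | 24 | 0.61 | 30 |
| 70% | 21 | 0.16 | 35 |
| 60% | 18 | 0.02 | 40 |

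**4. Cost of the rule itself.** Suppose 80% complete the first phase, which uses up the plan's allowance. Keeping available data leaves 30 × 0.80 = 24. Under removal the number is 24c, where c is the assumed proportion of those who go on to complete the second phase: 21.6, 19.2 and 16.8 for c = 90%, 80% and 70%. Restoring 24 needs 24/(0.8c), that is 34, 38 and 43 enrolled.

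For a pooled two-group SD with n − 2 degrees of freedom, the upper 95% limit is the estimate times √(df/χ²(0.025, df)). That factor is 1.42 at n = 24, 1.48 at n = 20 and 1.55 at n = 17.

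**5. Timing.** With the first visit on day 0 and participation ending on day 28, a second visit on day d has a full 7-day window only if d + 7 ≤ 28, so d ≤ 21. A return on days 22 to 28 satisfies the eligibility rationale but leaves a shortened window. The document does not say how often this would happen.

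**6. Selection, as illustration only.** Assumptions: untransfused SD 1, within-person correlation 0.5, true mean effect 0.5 with SD 0.5, and 20–27% dropout after the first period. Dropout is more likely at low first-period activity in the no-transfusion-first sequence and at high activity in the transfusion-first sequence. No baseline adjustment is made.

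| Shift in log-odds of dropout per SD | Within-person estimate, completers | First-period contrast, completers | First-period SD, no-transfusion-first completers |
|---|---|---|---|
| 0 | 0.50 | 0.50 | 1.00 |
| 0.5 | 0.44 | 0.27 | 0.98 |
| 1.0 | 0.37 | 0.05 | 0.94 |
| 1.5 | 0.32 | −0.16 | 0.89 |

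With everyone kept, the first-period contrast is 0.50 in every row. When dropout is unrelated to activity there is no bias. Otherwise its size and direction follow from the assumed mechanism.

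**The case against.** The strongest reply is that the rule may be meant narrowly. It speaks of data loss caused by partial completion, and that term is not defined. A second visit on day 24 shortens a window, but the model takes daily values, so the participant need not be removed. The attrition allowance already names schedule changes, so some such losses were foreseen. This stands as far as it goes, but as written the rule still covers someone who completed only the first phase.

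A reader might infer that the 28-day period makes partial completion common. An even spread of second visits over days 7 to 28 would put (28 − 21)/(28 − 7) = one third after day 21. That spread is an assumption. The article expects return within 28 days to be the norm, calls 28 days the expected duration in its description of the weekly calls, and sets its one-week minimum from the last trial transfusion, which a no-transfusion-first participant has not had. The claim is not supported.

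A reader might also infer that the rule demonstrably selects on the outcome. Admissions and non-study transfusions are listed only as exploratory measures, and nothing says they cause non-completion. Schedule changes or reluctance to wear the monitor are equally possible. Selection is a risk here, not a finding. Nor is 30 a miscalculation: the text says the number is raised by 25%, and it is.

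On feasibility, the article commits to CONSORT pilot reporting and keeps screening logs, so inflated rates would arise only if the reduced cohort were the denominator.

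**Conclusion.** The concern holds in this form: the removal rule contradicts the first-phase basis of the sample size and deletes data that the planned model can use. This follows from the text and needs no assumption beyond reading the rule as written.

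Its size depends on completion rates that the document does not give. The target of 24 is fairly safe at 90% two-period completion (0.97), little better than even at 80% (0.61) and unlikely at 70% (0.16). Selection bias and a distorted standard deviation are plausible because retention is settled after randomization; if dropout is unrelated to activity, the harm is lost precision only. The trial is a pilot with no power target, so what is threatened is the quality of the standard deviation, the effect signal and the feasibility figures.

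**What to change.** Replace the removal sentence under Data monitoring with wording such as:

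> Every randomized participant with evaluable post-visit device data remains in the primary random effects model with all available visits. An analysis restricted to participants completing both periods is a sensitivity analysis. Partial completion is reported by sequence, and feasibility rates use all enrolled participants as the denominator.

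Define partial completion, state in advance how many valid days make a visit evaluable, and bring Data monitoring, Primary analysis and Sample size considerations into agreement. Keeping all visits removes the selection made by the rule; it does not protect against dropout that depends on unobserved values.

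Device wear should not be cut below 28 days. Stopping it 7 days after an early second visit would remove data that the planned 28-day sensitivity analyses use. At most, wear could continue to 7 days after a late second visit. Because the second visit has no upper time limit, that extension would need a stated end.

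The analysis change costs wording only. The optional extension costs a longer wear period and added weekly calls for late returners.
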